## Abstract

**Background:**

Although many people with chronic low back pain (LBP) improve following conservative treatment, one in five will experience worsening symptoms after discharge from treatment and seek health care again. The current LBP clinical care pathway in many health services lacks a well-integrated, systematic approach to support patients to remain physically active and self-manage their symptoms following discharge from treatment. Health coaching can support people to improve physical activity levels and may potentially reduce health care utilisation for LBP. The primary aim of this study is to evaluate the effect of introducing a coordinated support system (linking hospital outpatient physiotherapy services to a public health coaching service) at discharge from LBP treatment, on the future use of hospital, medical, and health services for LBP, compared with usual care provided at discharge.

**Methods:**

Three hundred and seventy-four adults with chronic non-specific LBP will be recruited from the outpatient physiotherapy departments of public hospitals in New South Wales, Australia. Participants will be individually randomised to a support system (*n* = 187) or usual care group (*n* = 187). All participants will receive usual care provided at discharge from treatment. Participants allocated to the support system will also receive up to 10 telephone-based health coaching sessions, delivered by the Get Healthy Service®, over a 6-month period. Health coaches will monitor and support participants to improve physical activity levels and achieve personal health-related goals. The primary outcome is the total number of encounters with hospital, medical, and health services for LBP, at 12 months from baseline. A within-trial economic evaluation will quantify the incremental costs and benefits of the support system from a health system perspective, to support reimbursement decision making.

**Discussion:**

This study will establish the effect of a coordinated support system, introduced at discharge from treatment, on the future use of hospital, medical, and health services for LBP and various health outcomes.

**Conclusion:**

Innovative community-driven solutions to support people with chronic LBP after discharge from treatment are urgently needed. Study findings will help inform health care policy and clinical practice in Australia.

**Trial Registration:**

Prospectively registered on the Australian New Zealand Clinical Trials Registry (ACTRN12620000889954) on 10/09/2020.

**Supplementary Information:**

The online version contains supplementary material available at 10.1186/s12891-021-04479-z.

## Background

Low back pain (LBP) is the leading contributor to disability in Australia and globally [1, 2]. In Australia, nearly 4 million individuals report LBP at any one time [3] and the total cost of treatment exceeds $9 billion annually [4]. Within the current model of care for LBP in most countries, patients are commonly referred to primary care for treatment, including physiotherapy services (private clinics and hospital outpatient departments) [5, 6]. Although many people with LBP continue to improve following discharge from treatment, with approximately one third of individuals recovering within the first 9 months [7], one in five people experience recurrence of pain [8, 9] and resort to seeking further care within 12 months [10, 11]. For patients discharged after receiving treatment for LBP from hospital outpatient physiotherapy departments, this extra care may include additional pain medication intake, re-entry to the hospital system for further outpatient physiotherapy treatment, presentation to the emergency department, or surgical intervention.

In Australia, local hospital networks are responsible for managing and linking public hospitals, health institutions, and health services across defined geographical areas [12]. This includes the provision of hospital-based outpatient physiotherapy services for people with LBP. In the Australian state of New South Wales, 15 local hospital networks (called local health districts) service a total population of 8.2 million people, across eight metropolitan and seven rural and regional locations. In the Western Sydney Local Health District, an ethnically and culturally diverse metropolitan region, the rate of re-presentation to hospital services (i.e., physiotherapy clinics, emergency departments, pain clinics, neurosurgical clinics) within 1 year after discharge from outpatient physiotherapy treatment for LBP is 21% (unpublished New South Wales hospital data). The high rate of re-presentation constitutes a financial burden of $AUD744,000 yearly in direct costs in this local health district alone. Extrapolating these estimates across all local health districts within New South Wales, the cumulative financial and resource burden of re-presentations following discharge from hospital outpatient physiotherapy treatment is undoubtedly substantial.

The decline in clinical outcomes and the additional use of care (i.e., hospital, medical, and health services) for this subset of the LBP population is likely to be amplified by the lack of an integrated, systematic, local health district-driven approach to support patients to self-manage their condition once physiotherapy treatment ceases. After a series of consultations with senior musculoskeletal clinicians and consumer groups representing patients with LBP in Sydney, Australia, we identified that the lack of a coordinated support system at discharge is considered a strong factor driving the pattern of patients returning to hospital for further treatment (unpublished New South Wales hospital consumer committee report). Patients who participated in focus groups expressed concerns regarding the overload of information delivered abruptly prior to discharge from treatment, as well as the lack of ongoing support available. As a result, patients reported poor confidence for self-management of symptoms and maintenance of positive health behaviours (i.e., adherence to exercise). The integration of a simple, low-cost but well-structured post-discharge support system into the care pathway of chronic LBP is likely to improve outcomes.

Health coaching is a behavioural approach that aims to support individuals living with chronic conditions to adopt sustainable health-promoting behaviours and improve their quality of life [13]. The approach is strongly grounded in evidence-based behaviour-change theories such as Social Influence Theory and the Trans-theoretical Model [14], and typically involves a qualified health coach using motivational interviewing techniques to support patients in achieving collaborative goals and empowering self-management of symptoms [15–17]. Evidence supports that telephone-based health coaching can result in clinically important improvements in physical activity in patients with chronic LBP [18]. This is important because people with chronic LBP who engage in moderate to high-intensity leisure-time physical activity have better outcomes in terms of pain, disability, and quality of life, than those who fail to maintain adequate levels of physical activity [11, 19–21]. Our pilot study of a health coaching intervention for LBP has provided evidence that a telephone-based health coaching intervention is acceptable to LBP patients, can improve physical activity levels, and crucially, may reduce the rate of care-seeking for LBP by 38% [95% confidence interval 0.32 to 1.18] compared with usual care [11]. Thus, health coaching appears to have potential to support people with LBP to remain physically active and reduce their future use of health services for LBP.

The Get Healthy Information and Coaching Service® (Get Healthy Service) delivers a variety of telephone-based health coaching programs for adults with a range of health behavioural risk factors and health complaints in the Australian states of New South Wales, South Australia, and Queensland [22]. Introduced in 2009, this is a well-established and fully operational service, funded by state governments, which provides health coaching programs at no charge for state residents. The goal of the Get Healthy Service® is to improve and support an individual’s capacity to self-manage their own health and wellbeing. The service currently offers a Standard (health) Coaching module which aims to support participants with goal setting, motivation, confidence to overcome barriers, and achievement of sustainable lifestyle changes (i.e., increased physical activity levels, reduced sedentary behaviour). Previous studies have shown that the Get Healthy Service® is effective in improving moderate and vigorous physical activity levels and reducing behavioural risk factors for chronic diseases (i.e., weight, waist circumference, body mass index, nutrition-related behaviours) in the general population [23, 24]. Participants receive up to 10 individually tailored health coaching calls, delivered according to participant preference, over 6 months. The health coaching sessions are led by coaches with university-qualifications in allied health care (i.e., dietetics, exercise physiology), who monitor participants closely throughout the program to ensure they meet their goals safely. The sessions aim to compliment clinical care and offer accountability for treatment plans provided to patients by their clinicians prior to enrolment into the service. The service also has strong clinical governance and appropriate escalation pathways. The Get Healthy Service® is a viable and readily implementable solution that could be systematically integrated in the LBP clinical care pathway, potentially addressing the lack of support available after discharge from treatment across many regions in Australia.

There is only one published randomised controlled trial (RCT) which has evaluated the Get Healthy Service® in people with chronic LBP. The study investigated the effectiveness of a healthy lifestyle intervention (incorporating the Get Healthy Service®) in people with chronic LBP [25], and found no effect on pain intensity, disability, physical activity, or health care use (assessed as health care utilisation over the past 6 weeks preceding assessment) [25]. However, the lack of effect in the study was likely due to poor adherence with treatment, and importantly, the study only recruited overweight or obese patients identified from a waiting list for consultation with an orthopaedic specialist [25]. A protocol paper for a new study has been published for a RCT investigating a healthy lifestyle program involving consultations with a physiotherapist and dietician, provision of educational resources, and referral to the Get Healthy Service and a smoking cessation program [26]. The results of the trial have not been published; however, the protocol describes that study participants will be recruited from a mixed population of patients identified from primary and secondary care, and the general community. Further, the protocol does not describe any measurement of intervention effect on the use of medical or health services for LBP. No studies have investigated the effect of systematically integrating the Get Healthy Service® as a solution to support patients with chronic LBP immediately after discharge from hospital-based care.

This manuscript presents the protocol for a RCT and embedded qualitative study of a coordinated support system introduced after discharge from hospital-based physiotherapy treatment for chronic LBP. The support system will involve a structured referral pathway linking hospital-based outpatient physiotherapy services to a health coaching program, delivered by Get Healthy Service®, which has been tailored for chronic LBP. The primary aim of this study is to evaluate the effect of introducing a coordinated support system at discharge from LBP treatment, on the future use of hospital, medical, and health services for LBP, compared with usual care provided at discharge. The secondary aims of the study are: (i) to investigate the effectiveness and cost-effectiveness of the support system on improving pain, disability, physical activity levels, and quality of life in people with chronic LBP and (ii) to identify factors related to the intervention, context, individual, and implementation process which may contribute to intervention outcomes and to use these findings to inform development of an implementation plan for scalability.

## Methods

### Study design

This is a randomised, single-blind, parallel, superiority clinical trial with 1:1 allocation ratio to either a coordinated support system introduced at discharge from treatment for chronic LBP (involving a structured referral pathway linking hospital-based outpatient physiotherapy services to the Get Healthy Service®), or usual care group (usual care provided at discharge from treatment). We will conduct an embedded qualitative study with key stakeholders, involving a series of in-depth interviews with clinicians and trial participants, and one or more focus groups with health coaches and agents from Get Healthy Service®. The trial protocol has been designed according to the Standard Protocol Items: Recommendations for Interventional Trials (SPIRIT) statement (see Additional file 1) [27]. The study intervention has been reported using the template for intervention description and replication (TIDieR) checklist (see Additional file 2) [28]. The results of the trial will be reported according to the CONsolidated Standards Of Reporting Trials (CONSORT) statement [29]. The trial has been prospectively registered with the Australian New Zealand Clinical Trials Registry (ACTRN12620000889954).

### Participant timeline

Table 1 shows the assessments at each timepoint following the SPIRIT statement [27]. Figure 1 demonstrates the flow chart of the study.

**Table 1 Tab1:** Study assessments at specific time points

	STUDY PERIOD					
	Enrolment	Baseline Assessment	Allocation	Follow-up Data Collection^**a**^		
**TIMEPOINT***	*Week − 4 to − 1*	*Week 0*	*Week 0*	*Fortnightly**	*6 months*	*12 months*
**ENROLMENT**:						
Informed consent	X					
Eligibility screen	X					
Allocation			X			
**INTERVENTIONS**:						
*Support system*			X	X	X	
*Usual care only*			X			
**ASSESSMENTS**:						
*Use of hospital, medical, and health services for LBP*		X		X	X	X
*Self-reported physical activity levels*		X			X	X
*Objective physical activity levels*		X			X	
*Physical Function*		X			X	X
*Pain intensity*		X		X	X	X
*Disability*		X			X	X
*Quality of life*		X			X	X
*Self-management behaviours*		X		X	X	X
*Medication use*		X		X	X	X
*Sleep quality*		X			X	X
*Attitudes regarding use of pain medications*		X			X	X
*Beliefs about back pain*		X			X	X

^a^ From baseline assessment (week 0)

**Fig. 1 Fig1:**
[figure not shown]
Flow chart of the study

### Participants

We will recruit 374 participants with chronic non-specific LBP from outpatient physiotherapy departments of public hospitals in New South Wales, Australia. Consenting participants will be randomly allocated to either the support system (*n* = 187) or usual care group (*n* = 187).

#### Inclusion criteria

Potential participants will need to meet all the following inclusion criteria:
i)18 years of age or older;ii)presentation of non-specific LBP of at least 12-week duration, with or without leg pain but without radicular (e.g., reflex changes, motor loss) symptoms. Non-specific LBP will be defined as LBP without diagnosis of a specific cause, and the absence of serious spinal pathology or indicators of potentially serious conditions using ‘red’ flags;iii)recently discharged (< 4 weeks post-treatment) from outpatient physiotherapy treatment from a participating hospital site. This includes discharge from one-to-one physiotherapy care directly into the community, or from supervised group exercise programs offered by the outpatient physiotherapy department;iv)have adequate hearing and eyesight to participate safely in physical activity;v)independent ambulatory status, with or without a gait aid.

#### Exclusion criteria

Potential participants will be excluded if they have any of the following:
i)known or suspected serious spinal pathology (e.g., fracture, inflammatory disorder); diagnosis of specific LBP (e.g., sciatica, spinal stenosis grade 3 to 4);ii)co-morbid health condition(s) diagnosed by a medical practitioner that would prevent participation in physical activity or exercise programs;iii)fibromyalgia or systemic/inflammatory condition; currently pregnant or planning to become pregnant over the study duration;iv)inadequate English to complete outcome measures or participate in the health coaching intervention;v)spinal surgery in the past 12 months;vi)LBP caused by involvement in a road traffic crash in the last 12 months or ongoing compensation.

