### Monitoring contamination

The Get Healthy Service® is well-established and free to use for state residents. It is possible that participants in the usual care group may self-refer to the Get Healthy Service® and enrol in any of the health coaching programs offered. To minimise the risk of contamination, participants will be informed prior to study enrolment that those randomised to the usual care group will be asked to not participate in the health coaching intervention. Participants will also be informed that at the end of their participation in the trial (i.e., after completing their 12-month follow-up assessment), they will be offered the opportunity to enrol into the Get Healthy Service® and any of its programs. During the trial, participants will still be allowed to seek other forms of care or continue with the standard usual care provided to them by their physiotherapist at discharge from treatment.

If a participant in the usual care group self-enrols into any of the Get Healthy Service's® programs during the study period, we will not ask them to discontinue the program and will continue collecting data from them unless they choose to withdraw from the study entirely. At the conclusion of the study (i.e., after completion of the 12-month follow-up), a research team member will phone all participants in the usual care group to confirm whether they self-referred to any of the Get Healthy Service® programs during the intervention period. During this phone call, participants who express subsequent interest in the Get Healthy Service® will be offered enrolment into the service.

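### Current Get Healthy Service users are not excluded, so a control may already be receiving the coaching under test, and the end-of-study check would not detect it

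*Protocol article*

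**What the plan says.** In the Protocol article, Inclusion criteria begins "Potential participants will need to meet all the following inclusion criteria" and lists five items: age, chronic non-specific low back pain (LBP), recent discharge from outpatient physiotherapy, hearing and sight, and walking ability. Exclusion criteria begins "Potential participants will be excluded if they have any of the following" and runs to six items, the last being "LBP caused by involvement in a road traffic crash in the last 12 months or ongoing compensation". No item in either list concerns the Get Healthy Service or any other health coaching. Consent and screening describes a check of eligibility and medical safety, and names no further question about coaching.

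Background describes a service in operation since 2009 "which provides health coaching programs at no charge for state residents". Monitoring contamination repeats the point ("The Get Healthy Service® is well-established and free to use for state residents") and continues: "It is possible that participants in the usual care group may self-refer to the Get Healthy Service® and enrol". That section then makes three provisions:

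- Before enrolment, participants are told that anyone allocated to usual care will be asked not to take part in the coaching.
- If a control self-enrols during the study, "we will not ask them to discontinue the program", and follow-up continues.
- After the 12-month assessment, controls are phoned and asked whether they self-referred during the intervention period. Baseline assessment and Monitoring adverse events put that period at 6 months.

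Statistical analysis specifies intention to treat throughout.

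**The concern.** The experimental treatment already exists outside the trial, at no cost, for the population being recruited. The plan recognises that its use by controls threatens the comparison, but no eligibility rule addresses a person who is already in a coaching programme at screening.

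If allocated to usual care, that person has already had some of the coaching. If allocated to the support system, the person gains less than a newcomer would. Either way there is little contrast, and under intention to treat the person stays in the analysis. The effect is to move the IRR towards 1 in a superiority trial. Unlike later self-referral, this contamination can be known before randomisation and avoided there. Once the person is randomised, it cannot be removed without departing from intention to treat.

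**Working it through.** **Step 1: does anything in the article close the gap?**

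| Provision | Reaches a person enrolled before randomisation? |
|---|---|
| Inclusion and exclusion lists | No; no item on coaching |
| Consent and screening | No; eligibility and medical safety only |
| Pre-enrolment request to controls | Partly; it may stop further calls but cannot undo past ones |
| Rule for controls who self-enrol during the study | No; enrolment came earlier |
| End-of-study call | No; someone who joined before the trial can truthfully answer no |
| Covariate counting earlier treatments | Not identifiably; the article does not say that coaching is included |

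**Step 2: the plan's own figure.** Sample size calculation states 374 participants (187 per group), 90% power, the 5% level and an IRR of 0.70. The total cannot be reproduced exactly, because no dispersion parameter is given and the base rate of 0.2 can be read as a rate or as a log rate. This check does not need it. It takes 90% power at IRR 0.70 as stated and asks how that power moves.

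**Step 3: dilution.** Assumptions:

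- The test is two-sided (the article does not say).
- A share f of controls is currently enrolled. The documents give no value, so a range is shown.
- Those controls already have the full treated rate for all 12 months.
- The standard error of the log rate ratio stays the same.

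Calibration: 1.960 + 1.2816 = 3.2415, so the standard error is |ln 0.70| / 3.2415 = 0.3567 / 3.2415 = 0.110.

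With the uncoached control rate set to 1, the control mean is (1 − f) + 0.70f, so:

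- Observed IRR = 0.70 / [(1 − f) + 0.70f]
- Power = Φ(3.2415 × ln(IRR observed) / ln(0.70) − 1.96)
- Total needed to restore 90% power = 374 × [ln(0.70) / ln(IRR observed)]²

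Worked example at f = 0.05: 0.70 / (0.95 + 0.035) = 0.70 / 0.985 = 0.711. The power argument is 3.2415 × 0.3416 / 0.3567 − 1.96 = 1.144, which gives 87.4%.

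| f | Controls affected (f × 187) | Observed IRR | Power | Total for 90% |
|---|---|---|---|---|
| 0 | 0 | 0.700 | 90.0% | 374 |
| 1% | about 2 | 0.702 | 89.5% | 380 |
| 2% | about 4 | 0.704 | 89.0% | 387 |
| 5% | about 9 | 0.711 | 87.4% | 408 |
| 10% | about 19 | 0.722 | 84.2% | 447 |

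**The case against.** The case against has real force on several points.

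- **A safeguard exists.** A reader might infer that the contamination section deals only with people who join after randomisation. It does not: the request to controls is announced before enrolment and is not limited to new joiners. Nor does the article say that a control already enrolled would carry on unchallenged, since the no-discontinuation rule is written for self-enrolment during the study. The safeguard stands, but only as a partial one.
- **Past users keep a contrast.** A reader might extend the concern to anyone coached recently and ask for a 12-month look-back. Contents of the health coaching program allows re-enrolment after completion. A past user allocated to the support system can therefore have a new course, while a past user in usual care is asked not to. An exclusion for past use is a debatable trade against generalisability, and the documents do not require it.
- **The packages differ.** The trial arm adds a structured hospital referral, a physical activity goal and LBP-tailored content. Existing enrolment is similar to this but not the whole of it, so even current users may gain something.
- **Overlap with another trial is not shown.** Background mentions a trial involving "referral to the Get Healthy Service and a smoking cessation program". It gives neither sites nor recruitment dates, and the service covers three states.
- **Background use may belong to usual care.** For a policy question about adding a referral pathway, this is arguable. The plan, however, asks controls to stay out of the coaching, so it has already chosen a comparison without it.
- **Prior use may be recorded.** The baseline questionnaire is an additional file that is not shown and might ask. That would help description, but it would not supply an eligibility rule.
- **The dilution is conservative.** It cannot produce a false claim of superiority.

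**Conclusion.** The point holds for people currently enrolled in a Get Healthy Service coaching programme. Nothing in the published criteria keeps them out, and the stated contamination check would miss enrolment that began before randomisation.

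The size is unknown because the prevalence is unknown. The tabulated losses are upper bounds for each assumed share, because they give every current user the full IRR of 0.70 for the whole year. At 1-2% the loss is about one power point or less; at 5% power is about 87%, and at 10% about 84%. A reader might infer that the trial is seriously underpowered for this reason. The documents do not support that, because they give no figure for existing use among these patients. This is an inexpensive improvement to a design whose sponsor already treats coaching of controls as a threat. It is not a defect that undermines the trial.

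**What to change.** 1. Add one exclusion item: currently enrolled in a Get Healthy Service coaching programme. Ask about it at the screening call.
2. Record past use of the service at baseline, and do not exclude on it, so that its frequency and balance between groups can be described.
3. Reword the end-of-study question to controls so that it covers any use of the service up to 12 months, including enrolment that began before randomisation. This also picks up months 7 to 12, which a question limited to a 6-month intervention period leaves out.

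The cost is one eligibility line, one screening question, one baseline item and a reworded call script, submitted as a protocol amendment. The downside is that a small number of otherwise eligible patients are turned away. The planned total of 374 need not change.
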